## Methods/Design

The Glaucoma Initial Treatment Study (GITS) is a multi-centred, cluster randomised, controlled, clinical trial comparing two treatments for patients with POAG and XFG. Treating investigators and patients are not masked to treatment allocation due to the nature of the treatments; however, the QoL questionnaire administrators are masked to treatment allocation.

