### Interventions

Patients will be randomised 1:1 to treatment with either SLT or topical ocular hypotensive therapy, according to a stepped regimen (Figs. 1 and 2). If both eyes meet the inclusion criteria, the eye with the highest IOP will be enrolled in the study. However, both eyes will receive the same treatment initially. If both eyes have the same level of IOP, it will be at the investigator’s discretion to choose the study eye based on visual fields and optic disc evaluation.

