### Randomisation

Randomisation schedules developed by the Centre for Eye Research Australia (CERA) Melbourne, (Coordinating Centre), using a list of computer generated pseudo-random numbers are designed to yield an assignment ratio of 1:1. Randomisation, per person, will be stratified by clinical centre and type of glaucoma. The randomization number will be assigned to a patient sequentially according to the order of enrolment within the stratum. The treatment assignment form, contained in an opaque envelope will be filed in the patient’s ‘Unmasked study folder’ with the patient’s screening code completed on this form. Sites will then scan a copy of the treatment assignment and email this to the Coordinating Centre for its records. When the number of envelopes on site reaches only four remaining, the site will notify the Coordinating Centre, which will send more envelopes containing treatment allocations.

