### Allocation concealment

Each study site will receive a block of sequentially numbered, sealed, and opaque envelopes containing treatment allocation for either ‘SLT’ or ‘Drops’. Opaque envelopes will be opened in order of sequence per site. A unique study code will be assigned to each patient at randomisation, consisting of a three-digit randomisation number along with the patient’s initials.

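### The trial is labelled cluster randomised but is designed and sized as individually randomised, and its per-site envelope rule does not match its stratification by glaucoma type

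*Protocol article*

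**What the plan says.** All statements are in the protocol article.

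- **Methods/Design**, the defining design sentence: "The Glaucoma Initial Treatment Study (GITS) is a multi-centred, cluster randomised, controlled, clinical trial comparing two treatments".
- **Interventions**: "Patients will be randomised 1:1 to treatment with either SLT or topical ocular hypotensive therapy". One eye per patient is the study eye.
- **Randomisation**: "Randomisation, per person, will be stratified by clinical centre and type of glaucoma", with the number "assigned to a patient sequentially according to the order of enrolment within the stratum". The same section tells a site to ask for more envelopes when four remain on site.
- **Allocation concealment**: "Each study site will receive a block of sequentially numbered, sealed, and opaque envelopes containing treatment allocation" for either arm, and "Opaque envelopes will be opened in order of sequence per site".
- **Primary analysis**: the longitudinal models account for correlation among observations on the same subject. No other level of clustering is named. The example covariates include severity, visual field, age and gender, but not glaucoma type.
- **Sample size estimation**: 175 per group for an effect size of 0.3 with 80 % power at the 5 % level. No intracluster correlation, cluster size or design effect appears.
- **Planned subgroup analyses**: primary and secondary outcomes are analysed by glaucoma type (POAG and XFG). No other subgroup is listed.

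**The concern.** Two sets of statements cannot all be true.

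The first concerns the unit of randomisation. In a cluster trial, groups are allocated, and both the sample size and the standard errors must reflect correlation within groups. The label tells readers, and anyone pooling the result later, which variance is valid. A wrong label invites a correction for clustering that this trial does not need.

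The second concerns how allocations reach patients. Stratifying by centre and type requires a separate sequence for each combination, so each site would hold two. The Allocation concealment section describes envelopes only at site level, and the resupply count is also at site level. Followed literally, one sequence serves both types and stratification by type exists on paper only. If there are two series, a count on the site total lets one series run empty while the other still holds four or more envelopes.

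Type is the only planned subgroup factor, so balance by type is the property the stratification was meant to secure.

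**Working it through.** **1. Does the sample size assume clusters?**

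Inputs (Sample size estimation; two-sided 5 % from the Statistical analysis plan section): difference 0.156 logit, effect size 0.3, power 80 %. The implied SD is 0.156 / 0.3 = 0.52.

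n per group = 2 (z₀.₉₇₅ + z₀.₈₀)² / d² = 2 × (1.960 + 0.842)² / 0.3² = 2 × 7.849 / 0.09 = 174.4, rounded up to 175.

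This is the stated figure. The t-test version gives 175.4, rounded up to 176, which matches the article's figure for the AQoL-7D. A cluster calculation would multiply by 1 + (m − 1) × ICC, which exceeds 1 for any cluster size m above 1 and positive ICC. The stated number is obtained with that factor equal to 1.

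**2. Does any other section define a cluster?**

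| Section | Unit implied |
|---|---|
| Methods/Design | cluster (not defined) |
| Interventions | patient; one study eye each |
| Randomisation | person |
| Allocation concealment | patient; each site's envelopes hold either arm |
| Primary analysis | patient (within-subject correlation only) |
| Sample size estimation | patient (factor of 1) |

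Both eyes of a patient initially receive the same treatment, but only one is the study eye, so eyes within patients do not form clusters in the analysis either. One phrase stands against five sections.

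**3. Stratum order against site order**

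Order within centre-by-type strata gives two sequences per site; order per site, read literally, gives one. The resupply rule also works at site level. Nothing in the article mentions a series by type, and nothing rules one out.

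**4. What would one sequence per site cost in balance?**

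The article gives no XFG share, number of sites or permuted-block size, so all of these are assumed. The simulation used 8 sites of 48 patients (384) or 15 sites of 25 (375), close to the planned 2 × 193 = 386; XFG share 10 %, 20 % or 30 %; blocks of 4 or 6; and 1,500 runs per setting. The measure is the SD of the difference between arms in the number of XFG patients.

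| Scheme | SD of XFG difference, range over settings |
|---|---|
| No stratification, √(number of XFG) | 6.1 to 10.7 |
| One sequence per site | 5.8 to 9.3 |
| One sequence per site and type | 2.5 to 4.5 |

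A single site sequence gives little more control of type than no stratification at all.

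**5. Illustration, with an assumed 20 XFG patients in the whole trial**

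P(13:7 or more uneven) = 2 × P(X ≥ 13), X ~ Binomial(20, 0.5), = 2 × 0.132 = 0.26.

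Effect on precision within XFG: 1/13 + 1/7 = 0.220 against 1/10 + 1/10 = 0.200. The ratio is 1.10, so the standard error rises by about 5 %.

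**The case against.** The strongest reply is that this is one stray word and one compressed description. The Randomisation section gives the governing rule, and the Allocation concealment section may be a shorter account of the same scheme, with separate series by type left to the full protocol. The harm is also limited: a 13:7 split costs about 5 % in standard error, the subgroup analysis compares arms within type, and the Baseline characteristics section adds a strongly imbalanced variable in a sensitivity analysis.

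Much of this stands. Separate series are not excluded, so failure of the stratification is possible but not shown. The loss of precision is small. Two parts do not stand. The article does more than omit detail: it states an order of assignment in one section and a different order in the next. And the safeguard for imbalance reaches only a sensitivity analysis, because type is not named among the primary model's covariates.

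A reader might go further and infer from the label that the trial lacks a needed design effect and is underpowered. The documents do not support that. No cluster is defined, patients are allocated individually, and the article gives no inputs from which a design effect could be computed. Any such figure would describe a trial that is not being run.

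**Conclusion.** The point holds as an inconsistency in how the allocation is described. The word *cluster* is wrong: patients are randomised individually, and the sample size and analysis need no inflation for clustering.

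The stratum rule and the envelope rule conflict as written. Whether stratification by type was actually lost depends on how sites held their envelopes, which the article does not settle. If one sequence per site was used, balance by type was close to chance. The simulated figures and the 26 % rest on assumed XFG numbers, site numbers and block sizes, and show scale only.

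A reader might also infer that a single site sequence biases the treatment comparison. It does not: allocation remains random within site, and imbalance in type arises by chance. What is at stake is balance in the only planned subgroup factor and an accurate account of the randomisation. The correction should be made, but the point does not threaten the trial's validity.

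**What to change.** 1. In Methods/Design, delete *cluster* and state that GITS is a multi-centre, individually randomised (1:1), controlled trial.
2. Establish what sites actually did and make the Randomisation and Allocation concealment sections agree with it:
   - *Separate series by type*: say that each site held one numbered series for POAG and one for XFG, opened in order within series, with the four-envelope trigger applied to each series.
   - *One series per site*: say that randomisation was stratified by centre only, and remove type as a stratification factor.
3. In either case, name glaucoma type as a covariate in the primary model.

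The trial started in January 2013 and is expected to finish in December 2016. With 24 months of follow-up, enrolment would have to end by about December 2014, before publication in September 2015. Supplying new envelope series is therefore probably too late, and the remedy is accurate reporting plus adjustment. The cost is a change of wording, a query to sites and one extra covariate.

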### Inclusion and exclusion criteria

#### Inclusion criteria

Inclusion criteria are as follows:35 years of age and above.Previously untreated patients with either POAG or XFG that, in the investigator’s opinion, warrants IOP-lowering treatment.Visual field - mean deviation (MD) values between 0 and -12 dB at baseline in the study eye on the Humphrey Visual Field Analyser.Optic disc changes consistent with glaucoma including rim loss, nerve fibre layer defects (NFLD), and disc haemorrhages.

#### Exclusion criteria

History or evidence of glaucoma other than POAG or XFG.Advanced glaucomatous field loss with MD > -12 dB.History of use of topical or systemic ocular hypotensive medication(s).Previous intraocular surgery (including glaucoma laser or glaucoma surgery), with the exception of uncomplicated phacoemulsification that did not require additional intervention for complications.Iridotrabecular drainage angle anomalies.Evidence of moderate non-proliferative diabetic retinopathy or worse, neovascularisation or rubeosis iridis.Current use of a systemic corticosteroid, epinephrine or clonidine.Patients, who in the opinion of the investigator, are at high risk of suffering symptomatic vision loss and/or may require glaucoma surgery within the 2-year follow-up to the study.Patients who are pregnant or currently breastfeeding and/or planning to become pregnant within the study period.Patients who have a condition or are in a situation, which, in the investigator’s opinion may put them at significant risk or may interfere significantly with the patient’s participation in the study.

Written informed consent will be collected from each participant prior to inclusion in the study.

### Interventions

Patients will be randomised 1:1 to treatment with either SLT or topical ocular hypotensive therapy, according to a stepped regimen (Figs. 1 and 2). If both eyes meet the inclusion criteria, the eye with the highest IOP will be enrolled in the study. However, both eyes will receive the same treatment initially. If both eyes have the same level of IOP, it will be at the investigator’s discretion to choose the study eye based on visual fields and optic disc evaluation.

**Fig. 1 Fig1:**
[figure not shown]
Selective laser trabeculoplasty (SLT) treatment regimen: participants will follow a stepped treatment regimen, depending on their response to treatment. App=applications; BL=baseline; IOP=intraocular pressure; SLT=selective laser trabeculoplasty

**Fig. 2 Fig2:**
[figure not shown]
Topical medication treatment regimen: participants will follow a stepped treatment regimen, depending on their response to treatment. BL=baseline; IOP=intraocular pressure; SLT=selective laser trabeculoplasty

### Selective laser trabeculoplasty

For patients assigned to the SLT treatment arm, a single application of pilocarpine (1 %) and apraclonidine (1 %) or brimonidine (0.2 % or 0.15 %) will be instilled into the operative eye prior to the laser (Fig. 1). A frequency doubled, q-switched Nd:YAG laser emitting at 532 nm with a pulse duration of 3 ns, a spot size of 400 μm, and pulse energies ranging from 0.2 to 1.7 mJ, coupled to a slit lamp delivery system with a helium-neon laser aiming system will be used in all cases. Any mirrored gonioscopic lens that does not magnify is acceptable for use during the procedure. The laser will be focused on the trabecular meshwork using the HeNe aiming beams and a single laser pulse will be delivered at the 3 o’clock position. The laser energy will be increased or reduced by 0.1-mJ increments until fine ‘champagne’ bubbles are generated. During laser application, bubble formation will be monitored with each pulse to avoid excessive bubble formation and to avoid no observed response.

Initial 180° treatments of approximately 50 applications will be applied inferiorly from the 3 to 9 o’clock position. The total number of pulses delivered and the total amount of energy delivered will be recorded following each treatment. Participants will return for review of treatment response in 6 weeks from the baseline treatment and will then follow a stepped regimen, depending on their response to treatment. If a second SLT treatment is required, it will be applied over 180° from the 9 to 3 o’clock positions (superiorly). Treatment changes may also be initiated if there is an adverse event post-treatment and if this is considered severe enough to warrant a change in treatment.

### Topical ocular hypotensive therapy

Patients randomised to the topical medication treatment group will be initially prescribed, where possible, a prostaglandin analogue with one drop to be instilled in each eye (or the study eye only if only one eye is enrolled) once daily (Fig. 2). We will instruct patients on how and when to instil their drops and stress the importance of adherence. Patients will return for review of treatment response 6 weeks from the baseline initiation of treatment and will follow a stepped regimen, depending on their response. We will change treatment if there is an adverse event that is considered severe enough to warrant such change or if there is progression in visual field loss or optic disc changes. Treatment response will be defined as follows:Successful response ≥25 % IOP reduction compared with baselines.Partial response = 10-25 % IOP reduction compared with baselines.No response = ≤10 % IOP reduction compared with baselines.

If patients have crossed over with both treatment regimens, they will exit the trial with further management at the discretion of the treating doctor (Figs. 1 and 2).

Based on the grading system developed by the Collaborative Initial Glaucoma Treatment Study (CIGTS) [35], optic discs will be clinically analysed for the following characteristics: (a) vertical and horizontal central cup to disc ratio; (b) focal and diffuse thinning of neuro-retinal rim; (c) presence of a disc haemorrhage; (d) nerve fibre layer defects; and (e) extent of peripapillary atrophy. If a change in treatment is deemed necessary and urgent, it may be initiated by the site investigator although the images would be reviewed by the Optic Disc Outcomes Committee (ODOC), masked to the treatment allocation (and initially the temporal sequence of the photos) to validate treatment change. For all disc changes considered non-urgent, these images will be referred to the ODOC where it will be the final arbiter on the presence/absence of optic disc changes and any alteration to treatment regimens. Visual field progression will be defined according to the following criteria identified by the Glaucoma Progression Alert on the Humphrey Visual Field result:Possible progression = 3 or more points show deterioration on at least 2 consecutive visits.Likely Progression = 3 or more points show deterioration on at least 3 consecutive visits.No progression detected = none of the above conditions is met.

At each visit, the patient’s visual field results will be reviewed and evidence of progression will be initially determined by the Guided Progression Analysis (GPA) alert and the site investigator. If the alert message is that of ‘Possible Progression’, then the visual fields will be forwarded to the Visual Field Outcomes Committee (VFOC), masked to the treatment administered to the patient. This committee will make the final determination on the presence/absence of progression and change to treatment regimens. If, however, the alert message is that of ‘Likely progression’, the investigator is permitted to change/alter treatment and then refer the fields to the VFOC to confirm this progression.

### Randomisation

Randomisation schedules developed by the Centre for Eye Research Australia (CERA) Melbourne, (Coordinating Centre), using a list of computer generated pseudo-random numbers are designed to yield an assignment ratio of 1:1. Randomisation, per person, will be stratified by clinical centre and type of glaucoma. The randomization number will be assigned to a patient sequentially according to the order of enrolment within the stratum. The treatment assignment form, contained in an opaque envelope will be filed in the patient’s ‘Unmasked study folder’ with the patient’s screening code completed on this form. Sites will then scan a copy of the treatment assignment and email this to the Coordinating Centre for its records. When the number of envelopes on site reaches only four remaining, the site will notify the Coordinating Centre, which will send more envelopes containing treatment allocations.

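### As described, the patient's code is entered only on the form inside the envelope and the Coordinating Centre is told only afterwards, so commitment before opening is neither enforced nor independently verifiable

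*Protocol article*

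**What the plan says.** Methods/Design states that "Treating investigators and patients are not masked to treatment allocation due to the nature of the treatments"; only those who administer the quality-of-life questionnaires are masked.

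Under Allocation concealment, "Each study site will receive a block of sequentially numbered, sealed, and opaque envelopes containing treatment allocation", and "Opaque envelopes will be opened in order of sequence per site". The three-digit study code is given at randomisation.

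Under Randomisation, the assignment form sits in an opaque envelope and is filed in the patient's unmasked folder, with the patient's "screening code completed on this form". The next step is "Sites will then scan a copy of the treatment assignment and email this to the Coordinating Centre for its records". Re-supply works as follows: "When the number of envelopes on site reaches only four remaining, the site will notify the Coordinating Centre". Unopened assignments are therefore normally on site.

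The same section says that numbers are given in order of enrolment within strata of centre and glaucoma type. The eligibility section requires written consent before a patient is included.

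**The concern.** Sealed envelopes conceal the allocation only if a particular patient is irrevocably tied to the next envelope before it is opened. In the steps described, the tie is made on the inner form, which can be written on only once the envelope is open. The only per-patient message to the Coordinating Centre follows. A site that opened the next envelope and then decided whose code to enter would produce the same form, scan and central record as a compliant site.

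Three features of this trial make that worth closing:

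- Entry depends partly on the investigator's opinion, both that treatment is warranted and in some exclusions.
- The primary outcome is patient-reported quality of life in patients who know their treatment.
- The protocol states in advance that it expects laser treatment to do better.

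Selective entry by arm would bias the primary comparison. Masking the interviewers does nothing about selection at entry.

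**Working it through.** **Order of steps.** The question is where the patient is first recorded relative to the opening of the envelope.

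1. Consent is obtained before inclusion. No notice to anyone outside the site is described.
2. The next number is assigned by order of enrolment. This states the intended order; no record that would prove it is described.
3. The envelope is opened in sequence at the site. The person who opens it is not named, and no entry on the sealed envelope is described.
4. The screening code is completed on the form from inside the envelope. This is the first described link between patient and assignment.
5. A scan is emailed to the Coordinating Centre for its records. This is the first described contact with it about that patient.

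Steps 1 and 2 set the rule. Steps 4 and 5 create the evidence, and both come after the arm can be seen. Sequential numbering fixes the order of the envelopes but not which patient meets the next one.

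**Illustration of what steering would do.** The protocol states no figure on this point, so there is none to reproduce. Inputs from Sample size estimation: 193 enrolled per arm, 15 % attrition, target effect 0.3 SD. Analysed per arm: 193 × 0.85 = 164.

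Assumptions with no source in the documents: the arm is known beforehand for a fraction f of patients, and their expected outcome is shifted by d SD in opposite directions in the two arms.

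Bias = 2 × d × f. With d = 0.5:

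- f = 0.10 gives 2 × 0.5 × 0.10 = 0.10 SD, a third of the 0.3 SD target.
- f = 0.05 gives 2 × 0.5 × 0.05 = 0.05 SD.

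Two-sided type I error = P(|Z + bias × √(n/2)| > 1.96), for a simple unadjusted comparison of two means.

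| n per arm | √(n/2) | Bias (SD) | Shift in Z | Type I error |
|---|---|---|---|---|
| 193 | 9.823 | 0.10 | 0.982 | 16.6 % |
| 164 | 9.055 | 0.10 | 0.906 | 14.8 % |
| 193 | 9.823 | 0.05 | 0.491 | 7.8 % |
| 164 | 9.055 | 0.05 | 0.453 | 7.4 % |

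The row with 164 and 0.10 SD is the more relevant of the larger-bias pair, because the primary analysis includes patients with 24-month data.

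**Is there enrolment left to change?** Trial status gives an expected finish of December 2016. With 24 months of follow-up, the last patient would have to enter by about December 2014, before publication in September 2015.

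**The case against.** The case for leaving this alone is substantial. Centrally generated, sequentially numbered, sealed, opaque envelopes opened in order are a recognised concealment method. The text makes assignment follow enrolment and puts consent before inclusion. It nowhere says that envelopes are opened early. Writing on the envelope before opening is the kind of operational detail that may sit in the full protocol, which is not shown. The analysis also adjusts for baseline severity, visual field, visual acuity, age and gender, which would remove part of any steering on measured status.

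All of that stands, and it limits the point. It does not remove it, because the article does more than omit a detail: it sets out a sequence in which both the identifying entry and the central record follow the reveal. Adjustment would not reach steering on unmeasured factors such as a dislike of drops.

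A reader might infer more in two ways, and the documents support neither:

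- That sites do know the next allocation in advance. The text shows only that such knowledge would leave no trace in the described records.
- That later assignments can be worked out by counting, because envelopes arrive as a block in an open trial. The article does not say that shipments are balanced, gives no block or shipment size, and may use the word to mean simply a batch.

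**Conclusion.** The point holds as a weakness of moderate importance: on the steps described, nobody outside the site can confirm that a patient was committed before the envelope was opened. Its real effect is unknown and may be nil. The 15 % and 17 % error rates are what a 0.10 SD bias would do. That bias rests on an assumed 10 % of patients steered by 0.5 SD each way, before any benefit from covariate adjustment. They show why the safeguard is worth having and are not an estimate for this trial. If site procedures already record the patient before opening, the defect is in the description only.

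**What to change.** Change the order in Randomisation and Allocation concealment for any enrolment still open. Before opening, the site writes the screening code, date and time on the outside of the sealed envelope and emails a scan of it to the Coordinating Centre. Alternatively, it emails the screening code, glaucoma type and confirmation of eligibility and consent. The existing scan of the assignment form then follows as now. If this is already practice, say so in the text.

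If enrolment has closed, compare the envelope sequence with consent dates at each site and report any discrepancy with the results. That check is partial, since it cannot show a patient who was deferred or never consented.

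The cost is one small extra step per patient by an email route that already exists, or a single reconciliation of records after closure. The sample size and the analysis are unaffected.
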